The efficacy of the intervention will be evaluated through outcomes measured on the children. Primary outcomes: (Aim 1 -PA): 1) Total time (minutes/day) of children’s moderate to vigorous PA and 2) Sedentary time (minutes/day). Secondary outcomes: (Aim 2 - Quality of diet): 1) Percentage of kilocalories (kcal) from added sugars, 2) Percentage of kcal from total fats and saturated fats, 3) Grams of fruits and vegetables, and 4) Number of snacks and kcal from total fats, saturated fats, and sugars coming from snacks. The 4 secondary outcomes will be measured by a 24-h recall, using the multiple pass method, applied to both mother and child and complemented with information regarding school breakfast and lunch in order to collect intake from an ordinary school day, covering both home and school.

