### Statistical considerations

Sample size and power calculations. The number of children enrolled in first grade in the 12 participating schools is 405 [(range: 11–55, mean = 35]. Assuming approximately 50% participation rate the aim is to enrol a minimum of 200 dyads, i.e. 50 per trial arm. Assuming an additional 20% attrition it is expected to collect data on 160 dyads (40 per arm, an average of 13 per school) (Fig. 1). Under a factorial ANOVA design with two factors (V and AB interventions), and each at two levels, the target sample size of *N* = 160 participants (40 in each of the four conditions) yields a 80% power to detect an effect size of 0.22 (Cohen’s f low/moderate) for any of the main effects (V, AB) and the interaction effect (V*AB); F test, α = 0.05.

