**Fig. 1 Fig1:**
[figure not shown]
Flow Diagram

An effect size of 0.22 corresponds to a change of 5 min/day in moderate/vigorous PA (within-cell SD = 11) and a change of 5.4 min/day of sedentary time (within-cell SD = 12) [44].

Statistical analysis will be conducted on an intention-to-treat principle. Therefore, all children will be included in the analysis regardless of the intervention uptake. However, the percentage of “attendance” (compliance) of each child/family can be measured and will be used for subsequent analyses to evaluate the intervention uptake by the families.

Baseline characteristics will be described using summary measures and mixed models (with school as random effect), selected depending on their distribution. The effect of the two interventions on each one of the study outcomes will be estimated using a generalized mixed linear model with link and distribution selected according to the type of outcome. The model will include “active breaks” (AB), “virtual” (V), active breaks and virtual (AB + V), time (baseline/end of study) and the interactions time*AB, time*V and time*AB + V as fixed effect. It will also include random effects: child (or mother) to account for the repeated measures, and school to account for the cluster induced by the school. The most parsimonious model for each outcome will be reported. The False Discovery Rate criterion will be used to correct for multiple testing in non-planned analyses.

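### Two unranked primary outcomes per intervention factor have no success rule, and the only stated multiplicity correction leaves planned tests out: up to 9.75% error per factor

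*Protocol article*

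**What the plan says.** The last paragraph under Environmental measures in the protocol article lists the primary outcomes as "Total time (minutes/day) of children’s moderate to vigorous PA and 2) Sedentary time (minutes/day". They are numbered, but nothing says that the numbering is a testing order or that success needs one or both.

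Statistical considerations powers the trial "for any of the main effects (V, AB) and the interaction effect (V*AB); F test, α = 0.05", on "160 participants (40 in each of the four conditions". The paragraph after Fig. 1 converts the target effect size into minutes per day for both outcomes, so the calculation is meant to cover both.

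The analysis text then states: "The effect of the two interventions on each one of the study outcomes will be estimated using a generalized mixed linear model". The intervention-by-time terms are given as "the interactions time*AB, time*V and time*AB + V as fixed effect". That makes three effect terms for each outcome.

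On multiplicity there is one sentence, also in the Abstract: "The False Discovery Rate criterion will be used to correct for multiple testing in non-planned analyses".

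**The concern.** Each factor has two chances at a primary success, each at 0.05, with no order, alpha split or joint requirement. The article does address multiplicity, but it confines the correction to analyses that were not planned. A later analysis plan that corrected the primary tests would go beyond the stated rule.

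At stake is what a single p-value below 0.05 means. If MVPA is null and sedentary time is nominally significant, the text allows that factor to be reported as effective on a primary outcome, and equally the reverse. The error rate behind the statement that active breaks work, or that the virtual programme works, is then above 5%.

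**Working it through.** **Inputs from the article**
- Two primary outcomes (end of Environmental measures).
- Three effects per outcome, alpha 0.05, N = 160 in four equal cells, f = 0.22, power 80% (Statistical considerations).
- MVPA difference 5 min/day with SD 11; sedentary difference 5.4 min/day with SD 12 (paragraph after Fig. 1).

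**Assumption.** The article gives no correlation r between the two outcomes. Both come from the same accelerometer, so they will be correlated. The tests are two-sided, so only |r| matters, and a range is shown.

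**Step 1. The stated power.** For a 1-df F test with 156 denominator df, the noncentrality is f² × N = 0.22² × 160 = 7.744. Power at 0.05 is 0.790. Using the stated differences, f = 5/(2 × 11) = 0.227 gives 0.815 and f = 5.4/(2 × 12) = 0.225 gives 0.807. The 80% is reproduced, on the article's own basis, which ignores clustering.

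**Step 2. One factor, two outcomes.** With both nulls true and each tested at 0.05, the independent case is 1 − 0.95² = 0.0975. With correlated outcomes (bivariate normal):

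| \|r\| | At least one false positive |
|---|---|
| 0 | 9.75% |
| 0.5 | 9.1% |
| 0.7 | 8.3% |
| 0.9 | 7.0% |

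**Step 3. All six planned primary tests.** In a balanced 2×2 the V, AB and V*AB contrasts are orthogonal. With all six nulls true and independent outcomes, the rate is 1 − 0.95⁶ = 0.265. The analysis terms can also be read as each arm against control, or as reference-coded terms with a product:

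| Reading | r = 0 | \|r\| = 0.7 | \|r\| = 0.9 |
|---|---|---|---|
| Factorial F tests | 26.5% | 23.0% | 19.7% |
| Each arm against control | 23.6% | 20.2% | 17.2% |
| Reference-coded with product | 21.4% | 18.3% | 15.6% |

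The range is therefore about 18–26% for correlations up to 0.7, and somewhat lower at 0.9. Without the interaction (four tests) it is 18.5% at r = 0 and 16.0% at 0.7.

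**Step 4. Power under the remedies.** Normal approximation by simulation, f = 0.22 for both outcomes, N = 160, so each test statistic has mean 0.22 × √160 = 2.78. Unadjusted power is about 79%.
- Fixed sequence: MVPA stays at 79%. Sedentary time needs both tests significant, which happens in about 68% of trials at r = 0.5 and 71% at r = 0.7.
- Holm: power for a given outcome is about 76% at r = 0.5 and 75% at r = 0.7.
- For comparison, one test held at 0.025 throughout (Bonferroni) has power 0.698. That is not the cost of Holm, which allows the second test 0.05 once the first has passed.

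**The case against.** The factors of a factorial trial may reasonably be treated as separate questions, each with its own 5%. The Discussion of the article supports this, since it wants the components judged separately as well as together. A significant interaction is also not in itself a claim that either component works. A reader might add up all six tests and conclude that the chance of a false primary claim is about one in four. The documents do not support that as the headline. It needs all six nulls to be true, near-independent outcomes, the orthogonal reading of the model terms, and the interaction counted as an efficacy claim. This part of the objection stands, and the point is sized per factor for that reason.

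It can also be said that 0.05 appears only in the power paragraph, that the analysis text speaks of estimating effects, and that a decision rule may sit in an analysis plan not shown. The first two are correct, but no other level appears anywhere. The third carries less weight, because the article does not stay silent on multiplicity: it states a rule and limits its reach. That the planned tests go uncorrected is an inference from that rule, but the natural one.

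A reader might extend the point to the secondary diet outcomes by counting their tests. Reporting secondary outcomes unadjusted, as non-confirmatory, is common practice, and the article claims nothing confirmatory for them. That extension would be a preference, not an error in the plan.

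**Conclusion.** The point holds at the level of the single factor. Two unranked primary outcomes, no success rule and a correction confined to non-planned analyses give a false-positive chance of up to 9.75% for each of AB and V, and about 7–9% at outcome correlations of 0.5 to 0.9. This assumes that either outcome alone can carry the claim, that both are tested at 0.05, and that the factor has no effect on either. The correlations are assumed, not documented.

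The six-test figure, at most 26.5%, is context and an upper value. It does not measure the defect, because leaving the two factors unadjusted against each other is defensible. The calculation concerns multiplicity only; clustering by school is a separate matter.

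**What to change.** Before the outcome data are analysed, add a few sentences to the analysis text:

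- Within each factor, MVPA is tested at 0.05, and sedentary time is tested at 0.05 only if MVPA is significant. Alternatively, Holm is applied across the two outcomes within each factor.
- The AB-by-V interaction is supportive.
- This holds the error at 5% per factor, not trial-wide. With two factors at 5% each, the chance of at least one false claim is still about 1 − 0.95² = 9.75% if they are independent.

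No extra data are needed. The fixed sequence leaves MVPA power unchanged but lowers power for sedentary time from about 79% to about 68–71% at correlations of 0.5–0.7. Holm treats the outcomes alike and lowers power for a given outcome from about 79% to about 75–76%. Both costs rest on the article's own unclustered calculation. The choice depends on whether MVPA is the leading outcome; if it is not, Holm is the fairer rule.

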## Discussion

To our knowledge, this is the first study to assess the impact of a communication and technology-based virtual intervention involving the parents of first grade children of public schools in Latin America and designed to prevent obesity in their families. If this resource should prove to be effective, and taking into account the widespread use of new communication technologies, it may contribute to the dissemination and promotion of health related habits, and ultimately aid in the fight against the challenge posed by obesity. The additional value of this tool is that it is amenable to be replicated and implemented at a distance, hence resulting cost effective.

Because all measurements will be obtained according to standard methodology and protocols, particularly the objective measures of PA with accelerometers, an added value of data to be reported by this study is that it is one of the few to provide unbiased information regarding dietary and PA patterns of first grade children of Argentina.

The theoretical model that pervades the program emphasizes accessibility and knowledge as critical pillars of change. The first one is addressed by providing an increased number of opportunities for practicing PA during school breaks; the latter in the provision of knowledge about healthy habits related to food intake and PA. Assessment of a theoretical model in which the components are split off and each one of them is evaluated both separately and then together with an objective methodology, will enable us to identify more precisely the value of each of the components that traditionally are included in a multi-component intervention aimed to prevent obesity. Developing countries are lacking information on interventions that are effective in the prevention of non-communicable diseases. Studies of this kind should be able to provide the scientific community and public health entities with tools that are both efficacious and evidence-based.

There is a general agreement about the importance of developing tools that contribute to prevent chronic diseases affecting global health. Regarding eating habits and behaviours linked to physical activity, the scientific community has agreed with the importance of beginning as early as possible, of including families, and if possible, the whole community in preventive strategies. An important barrier to the inclusion of parents in school preventive programs is their lack of time. Current technology appears to be an auspicious and affordable solution to reach them.

## Abbreviations

AB: Active breaks
AB + V: Active breaks and virtual
BMI: Body mass index
C: Control
GPAQ: Global physical activity questionnaire
HE: Healthy eating
PA: Physical activity
V: Virtual
WHO: World Health Organization
